### Randomization

Once written consent was obtained and baseline assessments completed participants were randomly allocated to one of the three Phase 1 groups (Figure 1) using a stratified randomized block design. Participants were stratified by gender and category of body mass index (25 to <30; ≥30 to <35 or ≥35 to 40) using blocks of variable length (either 3 or 6). Subjects received the next envelope in the sequence based on their stratified BMI and gender group. Envelopes were prepared ahead of time, sealed and distributed by a researcher not involved in data collection. Subjects were asked to not open their allocation envelope until they returned home. Subjects were re-randomized in the same way at the end of the weight loss phase to one of the two maintenance arms.

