### Data analysis

Analysis will be on an intention-to-treat basis. Analysis of covariance will be used to test for differences in weight loss between groups at 3 months. The model will be fitted using linear regression with weight at 3 months as the outcome variable, treatment group as the predictor variable of interest and weight at baseline included as a covariate. Other independent variables included in the model will be: gender, kilojoule intake at baseline and physical activity at baseline. Differences in weight loss between groups in the weight maintenance phase will be analysed using generalised linear mixed models (GLMM). The outcome in the model will be the individual's weight at the post treatment assessments, the main predictor of interest will be treatment group and baseline weight will be included as a covariate. Other independent variables included in the model will be: time, gender, kilojoule intake at baseline and physical activity at baseline.

Statistical significance of the primary efficacy analysis (at three months and 18 months) will be based on Hochberg's multiple testing procedure with the family wise error rate for each time point held at 2.5%. All secondary hypothesis tests will be performed using a 2-sided 5% significance level. In addition, linear regression and GLMM will be used to describe relationships among the various dependent and independent variables.

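### BMI category is a stratification factor but is missing from the covariates fixed for both models; the likely cost is a small loss of precision, not invalid inference

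*Protocol article*

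**What the plan says.** Protocol article, Randomization: "Participants were stratified by gender and category of body mass index", the bands being 25 to below 30, 30 to below 35, and 35 to 40. With two genders and three BMI bands there are six strata, filled "using blocks of variable length (either 3 or 6"). The scheme is reused for the second phase: "Subjects were re-randomized in the same way at the end of the weight loss phase to one of the two maintenance arms".

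Protocol article, Data analysis, 3-month model: weight at 3 months is the outcome, with "treatment group as the predictor variable of interest and weight at baseline included as a covariate". The list then closes: "Other independent variables included in the model will be: gender, kilojoule intake at baseline and physical activity at baseline".

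Protocol article, Data analysis, maintenance model: "the main predictor of interest will be treatment group and baseline weight will be included as a covariate", followed by "Other independent variables included in the model will be: time, gender, kilojoule intake at baseline and physical activity at baseline".

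Of the two stratification factors, gender is in both models. The BMI factor is in neither, whether as a category or as a continuous value.

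**The concern.** When randomization is balanced within strata, the analysis would normally carry the stratification factors. If a prognostic factor is left out, its between-stratum variation stays in the residual although the design has already balanced it. The model-based standard error is then somewhat too large, the test somewhat conservative, and some power is given away.

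This is not a detail waiting for an analysis plan. The article names the covariates one by one, keeps one design factor, drops the other, and adds two variables (energy intake and physical activity) that played no part in the randomization. What is at stake is efficiency and agreement between design and analysis. The direction of any error is conservative, so false-positive risk is not the issue.

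**Working it through.** **1. The plan's own figure.** The only number borrowed from the plan is the 48 participants per maintenance group (Sample size). The stated inputs (difference 1.5, SD 1.5, two-sided 0.05, 90% power) give n = 2 × (1.960 + 1.282)² × (1.5/1.5)² = 21.0, so 22 per group, or 23 with the t distribution. They do not give 48, which would have 99.8% power. That is a separate matter. Here 48 serves only as the arm size for the check.

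**2. Can baseline weight stand in for BMI category?** Not by itself: 90 kg is 90/1.80² = 27.8 kg/m² (lowest band) at 1.80 m and 90/1.60² = 35.2 (highest band) at 1.60 m. But two such people may well be a man and a woman, and gender is in the model. Within men, taking an assumed height of 1.78 m (SD 0.07), one SD either side gives 90/1.71² = 30.8 and 90/1.85² = 26.3. These still fall in different bands, but adjacent ones. Overall, under the assumptions in step 3, baseline weight and gender explain 73% of the variance of BMI and leave about 27%.

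**3. What does the omission cost when weight is the outcome?** Simulation with 6000 trials per scenario, two arms of 48, and blocks of 2 or 4 within the six strata. Assumptions not in the article: height 1.78 (SD 0.07) m in men and 1.64 (SD 0.065) m in women; BMI uniform on 25 to 40; residual SD of follow-up weight 4 kg; no true treatment effect; tests at two-sided 5%. The planned model is represented by baseline weight and gender; energy intake and physical activity are left out. The extra effect is the shift in follow-up weight per BMI category beyond what baseline weight predicts.

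| Extra effect per category | Mean SE, planned model | Mean SE, BMI category added | Ratio planned/added | Empirical SD, planned model | Type I error, planned model |
|---|---|---|---|---|---|
| 0 kg | 0.815 | 0.818 | 0.996 | 0.814 | 4.9% |
| 1 kg | 0.823 | 0.820 | 1.004 | 0.822 | 5.1% |
| 2 kg | 0.840 | 0.819 | 1.026 | 0.830 | 5.0% |
| 4 kg (extreme) | 0.907 | 0.819 | 1.107 | 0.873 | 3.9% |

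A hand check of the first row: 4 × √(2/48) = 0.816. Monte Carlo error is about 1/√(2 × 6000) = 0.9% for an empirical SD and √(0.05 × 0.95/6000) = 0.3 percentage points for type I error. From 0 to 2 kg the planned SE therefore agrees with the empirical SD to within about 1%, and type I error is nominal. At 2 kg the loss in sample-size terms is 1 − (0.819/0.840)² = 4.9% of participants. Only at 4 kg is the SE clearly too large.

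**4. Should baseline BMI replace baseline weight?** Not while weight is the outcome. With baseline BMI, gender and BMI category but no baseline weight, the residual SD rises from 4.0 to about 8.7 kg. The SE becomes about 8.7 × √(2/48) = 1.78, and simulation gave 1.77, roughly double.

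**5. If BMI were the outcome.** The abstract names BMI as the primary outcome. Uniform BMI on 25 to 40 has variance 15²/12 = 18.75, of which 27% (5.0) is unexplained by weight and gender. With an assumed follow-up scatter of 1.5 kg/m², the residual SD under the planned covariates is √(5.0 + 1.5²) = 2.7. It falls to about 2.0 with BMI category added and to 1.5 with baseline BMI included.

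**The case against.** The strongest reply is that the models already contain gender, which is the other stratification factor, and baseline weight, which is both the baseline value of the modelled outcome and the numerator of BMI. Given those two, BMI category may add nothing, and including it then costs slightly more than it returns (0.818 against 0.815). This largely stands, and it is why the point is minor.

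It does not remove the point. About a quarter of the variation in BMI remains after weight and gender, the omitted factor was chosen for the design, and adding it costs next to nothing if it proves uninformative.

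A reader might infer that the benefit of stratifying is lost altogether, or that the planned standard errors are wrong. The documents do not support that: with the covariates they list, the planned SE tracks the empirical SD over the plausible range. A reader might also infer from the declared BMI outcome that the loss is large. That holds only if BMI is put into the model with the weight-based covariates. Data analysis specifies weight as the outcome, and the mismatch with the abstract is a separate point.

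**Conclusion.** The omission is a fact of the text: BMI category stratifies the randomization and is in neither covariate list, so the analysis does not fully reflect the design. With weight as the outcome the likely consequence is small. The planned SE is about 0.4% smaller to 2.5% larger than with BMI category included, for extra effects of 0 to 2 kg per category, with no inflation of type I error. The loss reaches about 11% on the SE only if BMI category has a strong effect beyond weight (4 kg per category), and the error is then conservative.

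These sizes rest on the assumed heights, BMI distribution and 4 kg residual SD, none of which the article gives. The maintenance model was not simulated with repeated measures, nor the 3-month comparison with three arms. This is a minor efficiency point, not a threat to validity.

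**What to change.** Add BMI category as a three-level factor to both the 3-month ANCOVA and the maintenance mixed model, alongside gender. Use the category by which the participant was actually stratified at the randomization being analysed: the initial one for the 3-month comparison, and the re-randomization for the maintenance comparison. The article does not say whether the later strata rest on entry BMI or on BMI at that time, so the sponsor should state this from the allocation records.

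Keep baseline weight as the covariate while weight is the outcome. Replace it with baseline BMI only if the modelled outcome is changed to BMI, the declared primary outcome.

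The cost is two degrees of freedom, and in the simulations at most about 0.4% on the SE. No new data are needed.

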**Figure 1 F1:**
[figure not shown]
**Flow of participants into the three baseline groups of the web-based weight loss RCT**.

### Sample size

Based on having 90% power to detect a significant difference in BMI between weight loss groups of 1.5 kg/m^2^, assuming the SD of BMI is 1.5 and using a two-sided significance level of 0.05, a sample size of 48 participants (24 males and 24 females) is needed for each maintenance group at 18 months. This sample size is within the range of other web-based weight loss intervention studies [13].

## SP Health Weight Management Program

SP Health Co PTY LTD is a commercial online weight loss program provider, which runs a number of Internet-based programs in Australia, UK and Asia including The Biggest Loser Online Diet Club Australia http://www.biggestloserclub.com.au

### Weight loss and weight maintenance Interventions

#### Theoretical framework for development of online features

Achieving and maintaining weight loss requires behaviour change. Bandura's Social Cognitive Theory [14] proposes that behaviour change is influenced by environmental factors, personal factors, and attributes of the behaviour itself. This interaction is referred to as 'reciprocal determinism', as each factor may affect or be affected by the others. The online program targeted key mediators including self-efficacy (e.g. goal setting, self-monitoring of weight, body measurements, exercise and diet), outcome expectations (e.g. knowledge-based web components), modelling (e.g., interactive website features and demonstrations) and social support (i.e. forums, blogs, feedback, email and/or telephone contact).

### Phase 1 - Weight-loss interventions

The interventions are delivered online for 12 weeks, with new program content distributed to the user weekly for both programs. At the end of 12 weeks participants could choose to repeat the same 12-week weight-loss program, or continue for an additional 12 weeks with the accumulated program content all available, or transfer to weight-loss maintenance if they lost a minimum of 10% of their baseline weight.

#### Group 1 - Wait-list control

The initial 12-week waitlist control group was a separate control arm. These subjects were assessed at baseline and 12 weeks, and then re-randomized to Group 2 or Group 3. The time frame for the control was limited to 3 months as it is unrealistic to expect people who volunteer for a weight-loss study in anticipation of achieving weight loss to comply with waiting for longer than 3 months. They did not have access to the study website and were also asked to refrain from undertaking any other weight-loss program during this time.

#### Group 2 - Basic online program

These participants had free access to the study website for the duration of the project. This online program has the following features:

• Individualised daily Calorie targets to facilitate 0.5-1 kg weight loss per week, based on participants weight, height and activity level

• Online food and exercise diaries and search engines to facilitate entry of food data

• Weekly Calorie-controlled, low fat menu plans and grocery list

• Weekly physical activity plan according to exercise preferences

• Weekly educational tips and challenges

• Social support via online forums

• Daily and weekly calculations of energy balance and nutrition summaries referenced to recommended nutrient targets

• Weekly email newsletters notifying the user of new content relevant to their point in the program

• Self-monitoring of reported body weight, waist and hip girths, with automated weekly reminders for entering weight

• Goal setting options and graphical display of changes in body measurement data and body (BMI) silhouette.

#### Group 3 -Enhanced online program

These participants had access to the online program described above plus received automated, computer-generated, personalized feedback based on their diet and physical activity diaries, their use or lack of use of the standard website features, and the level of success of their weight loss.

This "enhanced" online program has the following features additional to the basic program:

• A personalised enrolment report (system-generated) which suggests weight loss goals and prioritizes key behaviours the user will need to change to be successful at weight maintenance

• Weekly automated (system-generated) personalized feedback for key elements of nutrition and physical activity levels based on entries made in the online diary, including strategies to help the user change unhelpful eating behaviours identified during enrolment.

• Weekly (system-generated) personalized feedback reporting on the level of success of their weight loss journey, and general use of website features,

• Reminder schedule for compliance to the diary, site visitations and a weekly weigh-in escalating with urgency (email, text messages and personal phone calls).

### Phase 2 - Maintenance of lost weight

This phase commenced at the completion of the weight loss phase.

#### Group M1 Basic maintenance of lost weight program

• Continued access to the online program for a further 12 months, including online forum access.

• Adjusted daily Calorie target for weight maintenance.

• Weekly menu plans and exercise programs according to individual preferences, adjusted for the user's maintenance Calorie target.

• Continuation of weekly educational tips and challenges based upon food, activity and lifestyle, including four consecutive weeks of maintenance-specific content.

• A certificate to celebrate the achievement of goal weight or reaching the maintenance phase.

• Weekly email and phone text prompts to continue entering body weight and other body measurements.

• Maintenance-specific feedback on weigh-ins including warnings if the user's weight is creeping up.

• Access to an online information page detailing evidence-based behavioural strategies to enhance the likelihood of weight loss maintenance (e.g., eat breakfast; continue to monitor diet and physical activity; follow a low fat, low energy dense eating plan; be active for one hour a day; limit take-away and fast food; moderate week-end eating; react quickly when weight gain is observed).

#### Group M2 Enhanced maintenance of lost weight program

• All of the M1 program plus the following:

• Initial "welcome to weight maintenance phase" phone call from a trained consultant.

• Weekly and monthly system-generated, personalized reports summarizing energy balance and weight loss progress, website activity, and achievement of nutrition and physical activity targets.

• Regular questionnaires to help the user identify and prioritize behaviors (diet, physical activity and lifestyle-related) that can help achieve weight maintenance and prevent rebounds.

• Continuation of email, text and phone reminders to self-monitor weight, diet and physical activity, adjusted for maintenance time frame.

• Specific "relapse" weight loss program if weight rebounds by more than 3% of their baseline weight, including an initial phone call from a trained consultant.

• Congratulation emails for successful maintenance of lost weight.

## Quality Control

Monitoring the quality of the trial is essential to ensure a robust study and maintain internal validity. Several procedures were employed to optimize the quality of the study and maximize validity and reliability of the program delivery and outcome assessments. These are described below.

### Assessor blinding

Assessors of the main outcome measures are blinded to participant group allocation. These include those conducting anthropometric measurements, blood pressure and collecting blood samples. Participants are asked not to inform data collection personnel of their group allocation.

### Written documentation

All written documentation, including assessment protocols and letters sent to participants were standardised and subject to institutional ethics committee approval.

### Training

Data collection personnel involved in the assessments were trained prior to the assessments. Where possible the same assessors were used for all assessments. Consultants from SP Health were also trained prior to commencing reminder and maintenance phone calls to ensure consistency. Phone logs were recorded for quality purposes.

### Regular Teleconferences

Members of the BLC research team participated in weekly teleconferences with SP Health, the organisation delivering the online programs for the first 6 months and then fortnightly until all subjects were in the maintenance of lost weight phase. All teleconferences were minuted for reference.

### Instrument calibration

In order to ensure accurate and consistent measurements, the study weight scale was professionally calibrated once a year and the height scale checked and recalibrated daily before measurements commenced.

#### Demographic Data

Questionnaires to obtain current medical conditions and medications and were completed by participants at each data collection session. Smoking status and postcode as a proxy for socio-economic status were collected once.

#### Measurements

Laboratory-based assessments took place in the Human Performance Laboratory at the University of Newcastle, Callaghan campus. Assessments occurred at baseline, 3, 6 and 18 months and an extra 9 months assessment for the control participants.

#### Anthropometry

**Height: **measured to 0.1 cm using the stretch stature method on a Harpenden portable stadiometer (Holtain Limited, Dyfed, Britain). Height was measured twice, with accepted values within 0.3 cm. A third measure was taken if measurements were outside the acceptable range. The average of the two acceptable measures will be reported.

**Weight: **measured in light clothing, without shoes on a digital scale to 0.01 kg (CH-150kp, A&D Mercury Pty Ltd, Australia). Weight was measured twice, with accepted values within 0.1 kg. A third measure was taken if measurements were outside the acceptable range. The average of the two acceptable measures will be reported.

**Waist circumference: **measured to 0.1 cm using a non-extensible steel tape (KDSF10-02, KDS Corporation, Osaka, Japan). Waist circumference was measured at two points (i) level with the umbilicus and (ii) at the narrowest point between the lower costal border and the umbilicus. Two measures were taken at each site, with accepted values within 0.5 cm. Further measures were taken if measurements were outside the acceptable range. The average of the two acceptable measures will be reported.

**Body mass index (BMI): **calculated from height and weight (kg/m^2^).

#### Dietary intake

Dietary intake is assessed using the Australian Eating Survey (AES). AES is a 120-item semi-quantitative FFQ, used previously in Australian youth up to 16 years [15] and currently being validated in both adult males and females. Portion sizes for individual food items were generated by the Australian Bureau of Statistics (ABS) [16] and unpublished data from the 1995 Australian National Nutrition Survey; or the "natural" serving size for common items such as a slice of bread. Subjects were asked about frequency of their consumption over the previous six months with frequency options ranging from 'Never' up to '4 or more times per day' but varying depending on the food item. Twenty-one questions related directly to the intake of vegetables and 11 questions related to fruit. Seasonal availability of some fruits will be considered in the nutrient analysis.

Nutrient intakes from the FFQ were computed from the most current food composition database of Australian foods available, the Australian AusNut 1999 database (All Foods) Revision 17 and AusFoods (Brands) Revision 5 (Australian Government Publishing Service, Canberra) to generate individual mean daily macro-and micro-nutrient intakes.

The AES includes questions about the total number of daily serves of fruit, vegetables, bread, dairy products, eggs, fat spreads, sweetened beverages and snack foods, as well as asking the type of bread, dairy products and fat spreads used. Twelve questions relate to food-related behaviours, including items on frequency of take-away food consumption and eating while watching television.

#### Eating behaviour

The Three Factor Eating Questionnaire-R18, (TFEQ-R18) is a self-assessment questionnaire to measure cognitive and behavioural components of eating in obese populations across three scales of cognitive restraint, uncontrolled eating and emotional eating [17]. The 18 items are coded on a four-point scale with higher values indicating the behaviour is expressed more frequently or the statement is more correct for the participant.

#### Physical activity

**International Physical Activity Questionnaire **(short form): data from this questionnaire was used to estimate total MET-minutes/week and to classify participants into either high, medium or low physical activity categories according to the IPAQ Scoring Protocol [18].

**Pedometers: **physical activity was objectively measured using pedometers (Yamax SW700; Yamax Corporation, Kumamoto City, Japan). At baseline, participants were instructed on how to attach the pedometers (at the waist on the right hand side) and asked to remove the pedometers only when sleeping, when the pedometer might get wet (e.g. swimming, showering) or during contact sports. Participants were asked to wear pedometers for seven consecutive days and keep to their normal routine. At the end of the day participants were instructed to record their steps on a pedometer record sheet and reset their pedometers to zero. Participants were instructed to record if they did an activity like cycling, swimming, contact sports or another activity that did not involve stepping and include details (type of activity and duration), or if they forgot to wear their pedometer for an amount of time. Participants will be included in all analyses if they completed at least four weekdays of pedometer monitoring. The average of existing days will be imputed for participants who have included at least four days of data.

